### Outcomes

#### Primary Outcomes

The primary outcome measure is change in the FMA. The FMA is a standardized assessment tool initially designed to measure motor function, sensation (light touch and position sense), balance, joint range of motion, and joint pain in the upper and lower extremities of poststroke patients [27]. More specifically, the motor function subsection assesses reflex activity, volitional movement, and coordination/speed. Only the total motor score (upper and lower extremities) will be used in this study. The score varies from 0 to 100 points, with 66 points for upper extremities and 34 for lower extremities. Higher values represent better motor function. The FMA has excellent reliability [28], and its validity [29] and responsiveness [30] have been demonstrated. The training procedure proposed to enhance standardization of the assessment [31] will be completed by both examiners and blind assessors. For RCT1, the primary outcome for comparison will be the change from T0 to T1, and for RCT2, the primary outcome for comparison will be the change from T1 to T2.

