### Sample Size

For RCT1, assessing the noninferiority of HABIT-ILE@home compared to HABIT-ILE on-site, the sample size was calculated using PASS (version 14.0.15; NCSS) for a noninferiority 2-tailed *t* test of the difference between two means. The primary outcome is the change in the upper extremity subscale of the Fugl-Meyer Assessment (FMA-UE) score from baseline to postintervention (T1-T0), with higher scores indicating better motor abilities. We defined the noninferiority margin (NIM) using a method that ensures both clinical and statistical relevance, rather than only relying on the minimal clinically important difference. We chose the NIM as 50% of the difference between the changes observed with the gold-standard treatment and an interventional control group. This method was chosen to provide a more stringent criterion for noninferiority, ensuring that any treatment deemed non-inferior demonstrates a real benefit for stroke patients. As no previous studies have investigated such changes after a HABIT-ILE intervention, the sample size calculation was based on the mean change observed after a CIMT intervention (+5.6 points at FMA-UE; SD 3.1) [13]. The non-inferiority hypothesis was defined as follows: the HABIT-ILE@home intervention will be considered noninferior if the improvement produced is no more than 2.8 points lower than that obtained with the on-site HABIT-ILE intervention on the FMA-UE. An α level of 0.05 and a 1-β level of 0.8 were used for calculation. Under these assumptions, sample size calculation defined a number of 17 participants per group, resulting in a total of 34 participants.

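### The RCT1 margin, SD and sample size are set on the upper-extremity Fugl-Meyer subscale, but the outcomes section says only the total motor score will be used

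*Protocol article*

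**What the plan says.** Under Sample Size, the RCT1 definition is explicit: "The primary outcome is the change in the upper extremity subscale of the Fugl-Meyer Assessment (FMA-UE) score from baseline to postintervention (T1-T0"). The design inputs that follow are on the same subscale. The reference is the "mean change observed after a CIMT intervention (+5.6 points at FMA-UE; SD 3.1"), and the home programme is noninferior if its improvement "is no more than 2.8 points lower than that obtained with the on-site HABIT-ILE intervention on the FMA-UE". The result is 17 per group, 34 in total. The RCT2 paragraph takes its expected gain from the same FMA-UE data and sets a difference of 1.4 points.

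Under Primary Outcomes, the measure is change in the FMA, and "Only the total motor score (upper and lower extremities) will be used in this study". The scale is then described: "The score varies from 0 to 100 points, with 66 points for upper extremities and 34 for lower extremities". That section applies the measure to both trials: T0 to T1 for RCT1, and T1 to T2 for RCT2.

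The Abstract and the Blinding Procedure section say only FMA, so they do not settle which score is meant. The RCT1 part of Statistical Analysis compares the lower bound of a 95% CI with the margin. It defines the margin for every outcome as half the difference between a gold standard and a control group, without giving a number for the total motor score.

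**The concern.** A noninferiority conclusion rests on comparing one confidence bound with one margin, both on the same score. Here the margin is fixed on one score and the analysis on another. A reader cannot tell which estimate will be set against 2.8 points, nor which score the 80% power refers to.

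The upper-extremity score is a component of the total, so both will be in the dataset. If the definition is still open when results by arm are seen, the choice of score could be made, or could appear to have been made, with knowledge of the answer. The superiority comparison in RCT2 is exposed in the same way, because its 1.4-point difference is also an FMA-UE figure.

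**Working it through.** **1. The two definitions side by side**

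| Item | Sample Size section | Primary Outcomes section |
|---|---|---|
| Score | FMA-UE | Total motor FMA |
| Range | 0 to 66 | 0 to 100 (66 + 34) |
| Reference change, SD | 5.6, 3.1 | none given |
| RCT1 margin | 2.8 | none given |
| RCT2 difference | 1.4 | none given |

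The range of 66 for the upper-extremity part is taken from Primary Outcomes. The margin is 2.8/66 = 4.2% of the subscale range and 2.8/100 = 2.8% of the total range.

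**2. Reproducing the stated 17 per group**

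The inputs are margin 2.8 and SD 3.1 (Sample Size), with "An α level of 0.05 and a 1-β level of 0.8 were used for calculation". A true difference of 0 is assumed, because the article states none.

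Normal approximation: n = 2 × (SD/margin)² × (z_α + z_β)².

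- One-sided 0.05: 2 × (3.1/2.8)² × (1.645 + 0.842)² = 15.2, so 16. The t-based calculation also gives 16.
- One-sided 0.025, which matches a 95% CI: 2 × (3.1/2.8)² × (1.960 + 0.842)² = 19.2, so 20. The t-based calculation gives 21.

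The stated 17 is therefore close to the one-sided 0.05 result, and only with FMA-UE inputs. The description "for a noninferiority 2-tailed" and the 95% CI in the analysis section point to the other row. That is a separate matter, but it means the baseline for any power comparison must be stated.

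Noncentral-t power, with noncentrality 2.8 / (SD × √(2/n)), at SD 3.1:

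- 17 per group: 82.4% (one-sided 0.05), 72.4% (95% CI rule)
- 24 per group: 92.5% (one-sided 0.05), 86.5% (95% CI rule)

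**3. What would follow on the total score (illustration only)**

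The article gives no SD for the total score. Assume a lower-limb change SD of 1.5 to 2.5 and a correlation of 0 to 0.5 with the upper-limb change, and keep the 2.8 margin purely to isolate the effect of the SD.

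SD_total = √(3.1² + SD_LE² + 2 × ρ × 3.1 × SD_LE)

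- SD_LE 1.5, ρ 0: √(9.61 + 2.25) = 3.44
- SD_LE 2.5, ρ 0.5: √(9.61 + 6.25 + 7.75) = 4.86

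| n per group, rule | FMA-UE (SD 3.1) | Total (SD 3.44) | Total (SD 4.86) |
|---|---|---|---|
| 17, one-sided 0.05 | 82% | 75% | 50% |
| 17, 95% CI | 72% | 63% | 37% |
| 24, 95% CI | 86.5% | 79% | 50% |

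Seventeen per group is what the plan expects to remain after about 30% attrition from 48. Twenty-four per group is the upper limit, if all 48 contribute full information.

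**The case against.** The therapy deliberately trains the trunk and lower extremities, so the total motor score may well be the intended endpoint, with FMA-UE borrowed for the calculation only because no HABIT-ILE data in stroke existed. This is a fair reading, and it means the article does not show which score is right. It does not remove the contradiction: the Sample Size section says outright that FMA-UE is the primary outcome, rather than using it as a stand-in, and the total score would still lack a numeric margin.

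It can also be said that the total score does have a margin, since the analysis section gives a 50% rule for all outcomes. That is correct as far as it goes: a rule exists, but no number. Whether the cited study would supply one for the total score cannot be checked here.

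Three stronger readings are tempting and are not supported.

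- A reader might infer that the mismatch cuts power from the stated 80% to 37–63%. Part of that gap comes from the 95% CI rule: FMA-UE itself has 72.4% power at 17 per group under it. The figures also use only the post-attrition sample, and they keep a margin that should not be carried over to the total score.
- A reader might infer that a lower-limb gain could readily hide an upper-limb deficit, for example −3.5 upper and +1.5 lower giving −2.0 in total, within 2.8. The decision uses the lower confidence bound, not the estimate. With SD 3.44, an observed −2.0 has a lower bound of −2.0 − 2.037 × 3.44 × √(2/17) = −4.4 at 17 per group, and −4.0 at 24 per group. Both fail. Dilution is possible in principle, but this case does not show it.
- A reader might infer that no upper-extremity result will exist. It is a component of the total and will have been collected.

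**Conclusion.** The contradiction stands and should be resolved before analysis. Both statements are complete and positive, the word only in the outcomes section excludes a joint reading, and no section reconciles them. The 2.8-point margin, the SD of 3.1 and 17 per group belong to FMA-UE; they do not apply to the total motor score. The RCT2 difference of 1.4 points has the same problem.

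The consequence for power is unknown, because the total-score SD and margin are not given. The ranges above rest on the assumed lower-limb SD and correlation, a true difference of 0 and a retained 2.8 margin. They show the direction and plausible size of the effect of added variance, not a derived loss. The finding does not depend on them.

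**What to change.** Before any analysis by arm, make the Sample Size section (both trials) and the Primary Outcomes section name one primary score. Recruitment and data collection are complete, so the choice should follow the approved protocol and the registration, not be made afresh.

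- **If it is FMA-UE**, which all the stated design inputs use: delete the sentence restricting the study to the total motor score, and report the total motor and lower-extremity scores as secondary outcomes.
- **If it is the total motor score**: state a margin derived for that score, restate the SD and power on that scale for RCT1, and restate the target difference, SD and power for RCT2. Do not apply 2.8 to the total. Report FMA-UE against 2.8 as a secondary analysis.

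Either way, record the date of the clarification and that it preceded any look at results by arm. No new data are needed, since the subscale is part of the score already collected. The first route costs wording only; the second also needs a margin derivation and a revised power statement. The sample can no longer be changed.

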#### Secondary Outcomes

The same secondary outcome battery will be administered at T0, T1, and T2 for both RCT1 and RCT2. For RCT1, secondary outcomes for comparison will be the change from T0 to T1, and for RCT2 the secondary outcomes will be the change from T1 to T2.

##### Body Structures and Functions

Anxiety and depression will be measured by the Hospital Anxiety and Depression Scale (HADS) [32]. The HADS is a 14-item self-perceived questionnaire (7 items for the anxiety subscale and 7 items for the depression subscale) asking participants to estimate their mood in the past week [33]. Each item is rated on a 4-level scale, leading to a total score ranging from 0 to 21 points for each subscale used. Higher scores indicate higher anxiety and depression. HADS has shown an excellent internal consistency in the stroke population [34].

Gross unimanual dexterity will be assessed by the Box and Block Test, which measures the number of blocks transported from one compartment of a box to another in a minute [35]. This tool shows excellent test-retest reliability and is sensitive to detect changes in stroke patients [36,37].

##### Activities

Upper extremity motor capacity will be measured by the 17-item version of the WMFT [38]. A total of 15 items must be performed as quickly as possible, with a 120-second time limit. A total of 6 items assess joint-segment movements while 9 items evaluate integrative functional movements. Each of these 15 items is rated on a 6-level scale, leading to a total score ranging from 0 to 75 points. Higher scores represent higher upper extremity motor capacity. The remaining 2 items involve measures of strength. The WMFT is considered a reliable and valid measurement tool [38].

Manual activity performance, defined as the ability to manage daily activities requiring the use of the upper extremities (whatever the strategies involved), will be assessed using the self-administered Abilities of the Hand (ABILHAND-Stroke) questionnaire. Patients will be asked to report their ease or difficulty in performing 23 bimanual activities. As a Rasch-built questionnaire, the measures which are linear correspond to the percentage of the full range scale expressed in logits, from 0% (low manual performance) to 100% (high manual performance). This questionnaire shows a high reliability and a good validity [39].

Balance will be measured by the Mini-BESTest, which is a shortened version of the Balance Evaluation Systems Test. A total of 4 main domains of balance (anticipatory postural adjustments, reactive postural control, sensory orientation, and dynamic gait) are evaluated through 14 items. Each item is rated on a 3-level scale, leading to a total score ranging from 0 to 28 points. Higher values indicate better balance. This test is considered reliable and valid [40].

Lower extremity capacity, including mobility, balance, and walking skills, will be assessed by the timed up and go test. From a seated position, the patient will be asked to stand up, walk 3 meters, then turn around, walk 3 meters, and sit down. The score (in seconds) is the time taken to complete the functional task. The timed up and go test is a reliable and valid test for stroke patients [41].

Walking endurance will be evaluated by the 6-minute walk test [42]. The patients will have to cover the greatest possible distance in 6 minutes in a 30 m hallway, without taking a break. The 6-minute walk test is a good measure of endurance, giving an idea of daily life performance. This test has excellent validity and reliability [41].

Locomotor performance, defined as the patients’ ability to move about effectively in their environment, will be measured by the ABILOCO-Stroke questionnaire. Patients will be asked whether they are able to perform 13 locomotor activities on a 2-level scale (impossible or possible). ABILOCO-Stroke shows good psychometric properties [43]. As a Rasch-built questionnaire, the measures which are linear correspond to the percentage of the full range scale expressed in logits, from 0% (low locomotor performance) to 100% (high locomotor performance).

Global activity performance, defined as the ability to manage daily activities requiring the use of the upper and/or lower extremities (whatever the strategies involved), will be assessed by the Activity Limitations Questionnaire (ACTIVLIM-Stroke) questionnaire. Patients will be asked to report their ease or difficulty in performing 20 daily activities. As a Rasch-built questionnaire, the measures which are linear correspond to the percentage of the full range scale expressed in logits, from 0% (low global performance) to 100% (high global performance). The questionnaire shows a high validity [44].

The self-perceived patient’s performance in functional goals and their satisfaction with achieved performance will be evaluated through the Canadian Occupational Performance Measure. Patients will be asked to estimate their performance and their satisfaction on a 10-level scale, from 1 (low performance/satisfaction) to 10 (high performance/satisfaction). The Canadian Occupational Performance Measure is a reliable, valid, and responsive outcome measure [45].

Global disability level will be classified using the mRS. This scale classifies stroke patients into 7 levels, from 0 (no symptoms) to 5 (severe disability: confined to bed, incontinent, and requiring constant nursing care and attention) and 6 (death) [46]. The scale has shown excellent test-retest reliability [47].

##### Participation

Satisfaction in activities and social participation will be assessed by the SATIS-Stroke questionnaire. Patients will be asked to rate their satisfaction in the achievement of 36 activities or social life situations on a 4-level scale. As a Rasch-built questionnaire, the measures which are linear correspond to the percentage of the full range scale expressed in logits, from 0% (low satisfaction) to 100% (high satisfaction). Excellent test-retest reliability has been shown [48].

Participation, defined as the patient’s involvement in life situations (chosen because they make sense to them) in which they interact with others or which are linked to social roles, will be measured by the Participation In Life Situations – Stroke questionnaire (PILS-Stroke). This tool, which is still under development, will generate linear measures (in percentage of the full range scale expressed in logits), from 0% (low participation) to 100% (high participation).

##### Personal Factors

Confidence after a stroke will be evaluated using the 27-item Confidence After Stroke Measure. This self-administered questionnaire consists of 9 items of self-confidence (ie, feeling confident in one’s abilities, qualities, and judgment), 8 items of positive attitudes (ie, being optimistic about situations, interactions, and oneself), and 10 items of social confidence (ie, feeling comfortable in social situations and in social acceptance). Each item is rated on a 4-level scale, leading to a total score ranging from 27 to 108 points. The higher the values, the higher the confidence. The Confidence After Stroke Measure has shown good psychometric properties [49].

##### Health-Related Quality of Life

Health-related quality of life after stroke will be evaluated using the 59-item Stroke Impact Scale (SIS) [50]. This self-reported questionnaire covers 8 main health-related quality of life domains: strength (4 items), hand function (5 items), (instrumental) activities of daily living (10 items), mobility (9 items), communication (7 items), emotion (9 items), memory/thinking (7 items), and participation/role function (8 items). Patients will be asked to estimate the difficulty they experience in completing each item on a 5-level scale. The SIS shows adequate to excellent reliability [51] and excellent validity [52]. The proxy-patient version of the SIS will also be completed by the caregiver [53]. For each domain, an ordinal score is calculated with the following formula: Transformed Scale = [(Actual raw score - lowest possible raw score) ÷ Possible raw score range] x 100. A composite physical subscale can be calculated by combining 4 of the physical domains.

##### Feasibility and Adherence to Treatment (Satisfaction Questionnaire)

A satisfaction questionnaire was developed to assess the feasibility of both the 2-week HABIT-ILE@home intervention and the 9-week HABIT-ILE@home follow-up, and to compare them with the HABIT-ILE on-site camp and nonspecific follow-up, respectively. Patients’ and caregivers/interventionists’ adherence to treatment will also be recorded through the satisfaction questionnaire. The development of this questionnaire was informed by the HABIT-ILE@home pilot study, in which the feasibility, acceptability, and perceived burden of the telerehabilitation approach were assessed using instruments derived from validated scales [54]. Specifically, the questionnaire integrates dimensions adapted from the System Usability Scale, the User Experience Questionnaire, AttrakDiff2, the Dimensions of Mastery Questionnaire, the Intrinsic Motivation Inventory, the Exercise Adherence Rating Scale, and the Exercise Therapy Burden Questionnaire. Based on this, the questionnaire used in the present trial assesses the following dimensions: REAtouch Lite interactive system features, caregivers’ ability to follow the therapy schedule, and to apply motor skill learning principles, caregivers’ compliance, patients’ motivation and involvement, patients’ compliance (perceived usefulness of the therapy, enjoyment, and burden of the therapy), and preferences regarding therapy modalities (remote, in-person, or hybrid). The same questionnaire structure was adapted for the on-site modality, ensuring comparability (eg, removal of virtual-related sections, rewording of items). The satisfaction questionnaire will be filled in by patients, caregivers, and/or interventionists (only for on-site at T1), at the end of each intervention phase (T1 and T2).

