### Aims and Hypotheses

This protocol comprises 2 randomized controlled trials (RCTs), hereafter referred to as RCT1 and RCT2, conducted in the same cohort of 48 adults with chronic stroke. The first trial (RCT1) aims to test whether a 2-week high-dosage HABIT-ILE telerehabilitation program (HABIT-ILE@home) is noninferior to a 2-week high-dosage on-site HABIT-ILE camp in improving motor function. We hypothesize that both interventions will lead to significant improvements in motor function, activities, and participation, and that the HABIT-ILE@home group will be noninferior to the on-site group when comparing changes from baseline to postintervention (T1-T0). We further hypothesize that HABIT-ILE@home will demonstrate higher self-perceived burden for caregivers but will show acceptable feasibility, adherence, and perceived efficacy.

The second trial (RCT2) aims to evaluate whether a structured 9-week specific HABIT-ILE@home follow-up program is more effective than a dose-matched nonspecific home-based follow-up in maintaining and further enhancing the improvements obtained after the intensive phase. We hypothesize that, over the follow-up period (T2-T1), participants allocated to the specific HABIT-ILE@home follow-up will show superior retention and/or additional improvements in motor function, activity performance, and social participation compared with those receiving the nonspecific follow-up. We further hypothesize that HABIT-ILE@home follow-up will demonstrate higher self-perceived burden for caregivers but will show acceptable feasibility, adherence, and perceived efficacy. All outcomes will be assessed at baseline (T0), immediately after the intensive 2-week intervention (T1), and after the 9-week follow-up period (T2).

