##### HABIT-ILE On-Site Camp (Control Group)

HABIT-ILE on-site intervention will be held in a rehabilitation center in Belgium. All participants will be in the same room. Each participant will benefit from an individualized intervention with one or two dedicated interventionists (occupational therapists, physiotherapists, or students of occupational therapy or physiotherapy) during the whole process. At the end of each day, a group activity will be performed with all the participants.

The therapeutic plan of each participant will be established, supervised, and adapted day after day by a team of supervisors (occupational therapist and/or physiotherapist specifically trained for the supervision of a HABIT-ILE intervention). The supervisors will coach the interventionists throughout the day to ensure the application of HABIT-ILE and motor skill learning principles. In addition, at the end of each treatment day, the supervision team will discuss the session and coach the interventionists to adapt the therapeutic plan and define the type of activities for the next day, in order to ensure goal-directed motor learning throughout the intervention.

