#### Feasibility and Adherence

For questionnaire items shared by both groups, between-group comparisons will use Wilcoxon rank-sum tests. Items specific to the home-based condition will be summarized descriptively.

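### For RCT1 at T1 the article does not secure a like-for-like test of its caregiver-burden hypothesis: shared items may set family caregivers at home against therapy staff or students on-site

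*Protocol article*

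**What the plan says.** Under Aims and Hypotheses, directly after the home versus on-site comparison of RCT1, the article states: "We further hypothesize that HABIT-ILE@home will demonstrate higher self-perceived burden for caregivers but will show acceptable feasibility, adherence, and perceived efficacy". The hypothesis is directional and comparative, and it concerns caregivers.

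The person delivering the therapy differs by arm. Under HABIT-ILE@home (Treatment Group) it is a relative, partner or friend without therapist training. Under HABIT-ILE On-Site Camp (Control Group) it is "one or two dedicated interventionists (occupational therapists, physiotherapists, or students of occupational therapy or physiotherapy"), and relatives are given no part in the sessions.

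The section on the satisfaction questionnaire says: "The satisfaction questionnaire will be filled in by patients, caregivers, and/or interventionists (only for on-site at T1"). It also says: "Patients’ and caregivers/interventionists’ adherence to treatment will also be recorded through the satisfaction questionnaire". It describes the on-site version as the same structure with adaptations, giving as examples the removal of sections on the virtual system and the rewording of items, and it asserts that this keeps the modalities comparable. The one listed dimension that names burden is "patients’ compliance (perceived usefulness of the therapy, enjoyment, and burden of the therapy").

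Under Statistical Analysis, Feasibility and Adherence: "For questionnaire items shared by both groups, between-group comparisons will use Wilcoxon rank-sum tests". Only items specific to the home condition are left to description.

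**The concern.** A test of caregiver burden by modality needs caregivers in both arms. If the people answering for the on-site arm are professionals or students at work, a difference, or its absence, reflects who answered as well as where the therapy took place. Someone doing a job or a placement and someone caring for a family member can rate the same item differently for reasons that have nothing to do with telerehabilitation.

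The load on relatives is one of the main questions about a home model in which they deliver most of the therapy, and the Discussion treats it as something that must be documented. A rank-sum result on mixed respondents could be reported as higher, similar or lower burden at home and be wrong in any of these directions.

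**Working it through.** The article gives no effect size, margin or power for caregiver burden, so there is no figure to reproduce. The check sets the sections side by side.

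1. **What must be estimated.** The hypothesis is about home caregivers relative to on-site caregivers at T1. Write it as H − C, where H is burden among home relatives and C is burden among on-site relatives.

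2. **Who answers.** Interventionists answer only for the on-site arm and only at T1. The adherence sentence joins them to caregivers as one slot. The article does not say whether on-site relatives answer as well.

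3. **Which items are shared.** The stated examples of adaptation are removing the virtual sections and rewording. The remaining dimensions about the person delivering therapy are keeping to the schedule, applying the motor-learning principles, and compliance. If kept in reworded form, these become items shared by both groups. On-site, the interventionist is the person who can answer them meaningfully, because relatives deliver nothing there.

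4. **What the stated test would then compare.** Let P be the on-site interventionists' response. The contrast for those items is

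   H − P = (H − C) + (C − P).

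   The first term is the modality effect. The second is the difference between relatives and professionals within the on-site setting. If only interventionists answer on-site, arm and respondent type coincide, C is not observed, and the two terms cannot be separated. The second term can take either sign. Rewording an item does not remove it.

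5. **Whether burden is among those items.** In the list of dimensions, burden appears only in the patient-compliance entry. No caregiver dimension names it. The hypothesis therefore has neither a fixed on-site comparator nor a named set of caregiver items.

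6. **Scale.** With 48 participants allocated 1:1, each arm has 48 / 2 = 24. One caregiver per home participant gives up to 24 responses. One or two interventionists per on-site participant gives 24 × 1 = 24 to 24 × 2 = 48 responses, assuming each completes a form for each participant. Planned time for a home caregiver is 6.5 h × 5 days × 2 weeks = 65 h, plus 1 h + 2 h of training, or 68 h. An on-site relative has 0 h of planned delivery. These hours show how different the roles are. They do not measure the bias.

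7. **Where it stops.** Interventionists do not answer at T2, so the respondent mismatch does not arise for RCT2.

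**The case against.** The strongest reply is that the quoted sentence does not exclude on-site family caregivers. Its parenthesis limits where interventionists answer, and its and/or wording lets caregivers answer too. Participants and Setting requires an available caregiver for every participant, whatever the arm, and the Health-Related Quality of Life section has the caregiver complete the proxy Stroke Impact Scale. This stands. A reader might infer that RCT1 cannot test its hypothesis at all, or that the arms have no type of respondent in common. The documents support neither.

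Second, the analysis section never says in words that caregiver answers are tested against interventionist answers. Home-caregiver items might be classed as specific to the home condition and simply described. This stands in part: the mixed comparison is an inference. It is the natural one, since the test rule covers all shared items, does not mention respondent type, and follows a claim of comparability.

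Third, the questionnaire itself is not shown. It draws in part on an exercise-therapy burden instrument, and the Patient and Public Involvement section mentions burden questionnaires, so caregiver-burden items may exist. That stands as well: their absence is not shown. What can be said is that the article ties none to the hypothesis.

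Fourth, an article may leave item mapping to a fuller document. That would answer a complaint about missing detail. Here the hypothesis, the respondents, the test rule and the comparability claim are all stated, and followed together they can give a misleading contrast.

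Finally, a reader might argue that even a comparison of family caregivers in both arms is pointless, because 68 planned hours against none makes the direction obvious. The documents do not require that view. An expected direction does not invalidate a randomised comparison whose size is of interest.

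**Conclusion.** The point holds in limited form. For RCT1 at T1, the stated respondents and the stated test do not secure a like-for-like comparison of caregiver burden. On the natural reading, the shared items about delivering therapy compare relatives with therapy staff or students, and no caregiver-burden items are named.

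This rests on two assumptions that the sponsor can check at once: that items about the person delivering therapy remain in the on-site version and count as shared, and that interventionists' answers fill that slot. If on-site family caregivers also answered the burden items, a valid test is available and only the wording needs correcting. If they did not, the between-arm hypothesis cannot be tested from the questionnaire as collected.

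No numerical bias can be given, because the documents report no burden scores. The matter is secondary: the Fugl-Meyer comparison, the noninferiority margin, the sample size and the patient-completed items are unaffected. It still merits correction, because acceptability to caregivers is a stated RCT1 hypothesis.

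**What to change.** The article reports that data collection is complete and that analysis has yet to start, so the rule can be set before results are seen. In the questionnaire section and in Statistical Analysis, Feasibility and Adherence:

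- State that interventionist responses are summarised separately and are never pooled with, or tested against, caregiver responses.
- Limit between-group rank-sum tests to the same respondent type in both arms: patients with patients, family caregivers with family caregivers.
- Name the items that measure caregiver burden. This would also serve the parallel RCT2 hypothesis.
- State whether on-site family caregivers answered those items at T1. If they did, test the RCT1 burden hypothesis on them and note that they had no delivery role. If they did not, report home-caregiver burden at T1 as an estimate with a 95% CI and claim no between-arm difference.

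The cost is wording, applied to data already collected. The downside is that the RCT1 caregiver-burden hypothesis may become descriptive.
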